#### Data management {19}

The data collected on paper forms or in the patient electronic medical record are regularly transferred to an approved electronic database by a designated clinical research coordinator. The data will be coded with the according patient identifier, once transferred to the electronic database.

Study personnel will be trained on all important study-related aspects. After inclusion and trial participation of the first patient and regularly thereafter, the quality and accuracy of data collection will be checked internally.

All study data are archived for 10 years after study termination or premature termination of the study. The source data and all trial material will be stored in the archive of the study clinic.

#### Confidentiality {27}

Trial and participant data will be handled with uttermost discretion and is only accessible to authorized personnel who require the data to fulfill their duties within the scope of the study. On the CRFs and other study-specific documents, participants are only identified by a unique participant number^2^. The participant identification list is kept in a locked place under the supervision of the principal investigator at the study site. Only encrypted data, which cannot be traced back to the individual study participant without knowledge of the identification list, will ever leave the study site. Furthermore, all collected data is stored on password and safety-back-up protected drives of the study clinic, which can only be accessed by authorized personnel. However, the data gathered is always traceable to the source data (e.g., patient medical records or questionnaires) at the study site, based on the accordingly documented patient identifier and the original collection date.

For quality assurance the sponsor, the Ethics Committee or an independent trial monitor may visit the research sites. Direct access to the source data and all study-related files is granted on such occasions. All involved parties keep the participant data strictly confidential^3^.

#### Plans for collection, laboratory evaluation, and storage of biological specimens for genetic or molecular analysis in this trial/future use {33}

Collected oral mucosa on day -7, for pharmacogenotyping at humatrix AG in Germany (Stratipharm®), is destroyed 3 weeks after completion of the analysis and only the genetic data remain. These are encrypted with the sample number for evaluation and thus assigned to a database (server without internet access). Only designated employees have access to the data and must comply with strict data protection regulations. The genetic data will be kept until withdrawal. The laboratory in Germany has standards equivalent to those in Switzerland. Results of the pharmacogenetic testing by Stratipharm are made available for the responsible clinical pharmacist at the study site through a web portal, which is password protected and therefore only accessible by authorized personnel. The genetic data assessed by Stratipharm will be coded with the according patient identifier once transferred to the CRF and archived after study termination for at least 10 years.

Collected blood samples, 4 ml EDTA whole blood, and 6 ml serum on days 14 and 28 are not identified by participant name but by a unique participant identifier. For processing and further analysis, the biological material is transferred using dry ice shipment when necessary, to the biobank Biopharmazie at the University of Basel. There, the blood samples and thereof isolated DNA and processed blood serum are appropriately stored between −20 and −80°C in a restricted area only accessible to authorized personnel. Laboratory personnel handling the biological material outside of the study clinic do not have access to the patient identification list and therefore cannot trace the samples back to the individual participants. The planned analysis includes further pharmacogenetic targets and substance blood concentrations using standardized and established methods (e.g., TaqMan® genotyping assays, direct DNA Sanger sequencing, and LC-MS/MS or HPLC). The results of these examinations are not taken into account for the study treatment decisions and will only be assessed after day 28.

The collected blood samples and thereof processed samples (DNA and blood serum) will be stored in the biobank Biopharmazie at the University of Basel until study publication or early study termination. However, if participants consent to the further use of the assessed and encrypted genetic data and biological material, these will be stored over a yet undetermined time period and for a yet undetermined use in the study clinic or in the Biobank Biopharmazie respectively.

### Statistical methods

#### Statistical methods for primary and secondary outcomes {20a}

The primary outcome of this study is the response rate at day 28 in study arms A and B. The response is defined as a reduction of the HAM-D17 score of at least 50% compared to baseline at day 0. Additionally, the following secondary outcomes are assessed: time to response, remission rate, overall change in HAM-D17 score, laytime in the clinic, change in BDI-II score, change in FIBSER score, and number of AEs related to antidepressant pharmacotherapy. For statistical analyses, the software packages of “IBM SPSS Statistics” and “GraphPad Software” are used. A descriptive statistics analysis for all variables is performed. Fisher’s exact test or *t* test is used to compare pairwise differences between groups and between baseline and follow-up visits as per data type. To measure the correlation between variables, the Spearman coefficient will be used. Significance level is two-sided, *α* = 0.05. For further statistical analyses, adjustments for confounding factors will be taken into account. Any deviation from the original statistical plan will be described and justified in the final trial report.

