### Objectives {7}

We hypothesize that it is beneficial to incorporate PGx information to guide drug selection and dosing in the treatment of depression, involving clinical pharmacists in processing and evaluating the PGx test results in the context of the individual patient history and current co-medication.

The primary objective of this clinical study is to compare the service of pharmacist-guided PGx testing with the current standard of care for antidepressant selection and dosing with regard to treatment outcome. Accordingly, the following null hypothesis results for the primary endpoint: Therapy response rates after antidepressant treatment for 4 weeks do not differ whether the service of pharmacist-guided pre-emptive pharmacogenetic testing was applied or not.

The secondary objectives are to compare tolerability of the antidepressant pharmacotherapy and overall duration of hospitalization between the intervention and standard care study arms.

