#### Relevant concomitant care permitted or prohibited during the trial {11d}

The introduction of a new antidepressant pharmacotherapy or augmentation strategy (e.g., lithium and the like) are not possible until after randomization when genotyping results are available (7±2 days after inclusion). However, the following measures can be taken in the interim: (1) if an antidepressant therapy has already been taken before entering the clinic, it can be continued during this period, and (2) additional supportive measures are possible, including sleep-promoting pharmacotherapy (e.g., benzodiazepines or low-dose trazodone, mirtazapine, trimipramine).

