#### Outcomes {12}

The primary endpoint is defined as the rate of response to the antidepressant therapy at the end of week 4 of the treatment phase. This time point was chosen based on the recommendations of the SGAD, which advise to assess clinical effectiveness after four weeks of antidepressant pharmacotherapy [3]. Moreover, the response is determined as a reduction in the Hamilton Depression (HAM-D) Scale score of at least 50% from the baseline score [18]. In this study, the 17-item HAM-D questionnaire (HAM-D17) is used.

Secondary endpoints will be assessed to further evaluate the clinical effectiveness of pharmacist-guided PGx testing as an intervention in antidepressant pharmacotherapy. Included are the following endpoints: (1) time to response—time span from the start of antidepressant pharmacotherapy until first assessed response (= HAM-D17 reduction of at least 50% compared to baseline), until end of week 4; (2) remission rate—HAM-D17 score ≤ 8, at week 4; (3) overall change in HAM-D17 score from baseline to end of week 4; (4) time till discharge—time span from admission to discharge from inpatient treatment, assessed up to 3 months; (5) patient depression self-rating—two weekly assessment with Beck-Depression-Inventory (BDI-II) questionnaire [19], until end of week 4; (6) side effect measure—weekly assessment of self-rated frequency, intensity, and burden of side effects (FIBSER score) [20], until end of week 4; and (7) Number of AEs related to antidepressant pharmacotherapy—severity grading ≥ 2 (using CTCAE version 5.0) [21] and causality to antidepressant pharmacotherapy assessed as possible, probable, or definite, until end of week 4.

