**Fig. 1 Fig1:**
[figure not shown]
Study procedures

**Table 1 Tab1:** Schedule of assessments

Day	Pre-study	Run-in phase		Treatment phase					Follow-up	Clinic discharge
	−8	−7	−7–0	0	7	14	21	28	35, 42..	
Informed consent for trial participation	**x**									
Eligibility (pregnancy test, drug screening, inclusion, & exclusion criteria)	**x**									
Buccal swab (Stratipharm®)		**x**								
Medical history (previous antidepressant therapies)			**x**							
Lab values (basic hematology, creatinine (eGFR), ASAT, ALAT, total bilirubin, gamma-GT, CRP, TSH, vit. B12, and vit. D)			**x**							**x**
Concomitant medication documentation			**x**	**x**	**x**	**x**	**x**	**x**	**x**	**x**
RANDOMIZATION (only if new antidepressant indicated)				**x**						
PGx pharmaceutical recommendation (only arm A)				**x**						
Start NEW antidepressant				**x**						
HAM-D17	**x**			**x**^**a**^	**x**^**c**^	**x**	**x**^**c**^	**x**	**x**	**x**
AE assessment (antidepressant therapy only)					**x**^**c**^	**x**	**x**^**c**^	**x**	**x**	**x**
FIBSER patient self-assessment				**x**^**a**^	**x**^**c**^	**x**	**x**^**c**^	**x**	**x**	**x**
BDI-II patient self-assessment				**x**^**a**^		**x**		**x**	**x**^**b**^	**x**
Blood sample collection (EDTA and serum)						**x**		**x**		

^a^Baseline scoring before the first intake of new antidepressant

^b^BDI-II assessed in two weekly intervals

^c^Only for study arms A and B

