##### Randomization and procedures for arms A and B

If after the run-in phase, at day 0 (±3 days), the treating physician assesses the adjustment to a new antidepressant pharmacotherapy as necessary, and the patient is randomized to either arm A (intervention group) or arm B (control group) (see Fig. 1).

In arm B, the treating physician alone, according to the current standard of care considering clinical factors only, will determine the selection and dosing of the new antidepressant pharmacotherapy. The treating physician and patient will be blinded to the results of the previously conducted pharmacogenotyping for patients randomized to arm B until day 28. For patients in arm B, results from prior pharmacogenetic testing will be interpreted by a clinical pharmacist and made accessible to the treating physician after day 28.

In arm A, a clinical pharmacist will process and evaluate the results from PGx testing (Stratipharm®) in context of the individual patient history as well as current co-medication and forward an individualized recommendation for antidepressant selection and dosing to the treating physician at day 0.

In both arms, the newly prescribed antidepressant pharmacotherapy intake is continuously documented and therapy response observed over a period of 28 days with weekly assessments of adverse events related to the antidepressant medication (using CTCAE version 5.0) and scorings of HAM-D17 (days 0, 7, 14, 21, and 28; ±3 days) as well as patient self-assessments of FIBSER score (days 0, 7, 14, 21, and 28; ±3 days) and BDI-II score (days 0, 14, and 28; ±3 days) (see Table 1).

If patients in either study group remain in the clinic after day 28 (±3 days), a weekly follow-up of HAM-D17, FIBSER, and two-weekly BDI-II are continued until discharge (see Table 1).

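### FIBSER is listed as weekly ratings but analysed as a change from a day-0 score that precedes the new drug: the within-arm change is not tolerability of the new therapy, and adjusting for day 0 is never less precise than subtracting it

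*Protocol article*

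**What the plan says.** Tolerability is a secondary objective. Objectives {7} sets out to "compare tolerability of the antidepressant pharmacotherapy and overall duration of hospitalization between the intervention and standard care study arms", so the question is one between arms.

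The FIBSER endpoint is then described twice:

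- Outcomes {12}, item 6: "side effect measure—weekly assessment of self-rated frequency, intensity, and burden of side effects (FIBSER score"), up to the end of week 4. Item 3 of the same list uses the word change for HAM-D17; item 6 does not.
- Statistical methods {20a}: "change in BDI-II score, change in FIBSER score, and number of AEs related to antidepressant pharmacotherapy". No visit is named for the change. The tests (Fisher's exact or t test) serve "to compare pairwise differences between groups and between baseline and follow-up visits as per data type".

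The section on arms A and B schedules "patient self-assessments of FIBSER score (days 0, 7, 14, 21, and 28; ±3 days"). Table 1, footnote a, fixes the day-0 rating as "Baseline scoring before the first intake of new antidepressant". Section {11d} describes what a patient may take until then: "if an antidepressant therapy has already been taken before entering the clinic, it can be continued during this period", and "additional supportive measures are possible, including sleep-promoting pharmacotherapy". Section {20b} says that no adjusted analysis is foreseen at present, while {20a} says that further analyses will take account of confounding factors.

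**The concern.** For HAM-D17 and BDI-II, day 0 measures the depression that is about to be treated, so a change from day 0 has a clear meaning. FIBSER rates side effects, and at day 0 the new drug has not been taken. The day-0 score can reflect an earlier antidepressant, no antidepressant, or sleep medication.

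Take two patients with the same side effects on the new drug. One comes from a badly tolerated earlier drug and shows an improvement. The other comes from no drug and shows a worsening. A mean change within an arm mixes such patients. Section {20a} provides in general terms for a test of baseline against follow-up. Applied to FIBSER, that test could be reported as good or poor tolerability of the chosen therapy, which it does not measure.

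Also at stake is the precision of the only patient-rated tolerability measure, and whether the ratings on days 7, 14 and 21 enter the main comparison. A level, a change to one visit and a mean over visits can give different answers from the same data.

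**Working it through.** **The plan's own figure.** The document gives no sample size or power for FIBSER, only 95 per arm for the primary endpoint (0.5 against 0.7, two-sided 5%, power 80%). Pooled formula: [1.96·√(2·0.6·0.4) + 0.84·√(0.25 + 0.21)]² / 0.2² = 93 per arm, with power 0.81 at 95. The figure reproduces closely, and 95 per arm is used below.

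**Assumptions.** The document gives no FIBSER SD, effect or correlation. I take an SD of 1 at day 0 and at follow-up, a correlation r between them, and a between-arm difference of 0.41 SD. That is the difference with about 80% power on a single follow-up rating: (1.96 + 0.84)·√(2/95) = 0.41.

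**Step 1: is the between-arm change biased?** Day 0 is rated before the new drug, so under randomisation its expectation is the same in both arms and it cancels. In a simulation of 20,000 trials per value of r, with a true difference of −0.41, follow-up and change both averaged −0.41 at r = 0.2, 0.5 and 0.7. The answer is no.

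**Step 2: precision.** Variances relative to one follow-up rating:

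- follow-up alone: 1
- change: 1 + 1 − 2r = 2(1 − r)
- follow-up adjusted for day 0: 1 − r²

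| r | Variance, change | Power, change | Variance, adjusted | Power, adjusted |
|---|---|---|---|---|
| 0 | 2.0 | 0.515 | 1.00 | 0.807 |
| 0.2 | 1.6 | 0.608 | 0.96 | 0.822 |
| 0.3 | 1.4 | 0.666 | 0.91 | 0.842 |
| 0.4 | 1.2 | 0.732 | 0.84 | 0.869 |
| 0.5 | 1.0 | 0.807 | 0.75 | 0.904 |
| 0.6 | 0.8 | 0.885 | 0.64 | 0.942 |
| 0.7 | 0.6 | 0.954 | 0.51 | 0.977 |

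Follow-up alone has power 0.807 throughout. The simulated standard errors agree: 0.145 (follow-up) against 0.183 (change) at r = 0.2, 0.145 against 0.145 at 0.5, and 0.143 against 0.112 at 0.7.

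**Step 3: where the change breaks even.** With SDs s0 (day 0) and s1 (follow-up), the change is noisier than follow-up if s0² − 2r·s0·s1 > 0, that is, if r < s0/(2·s1). For s0/s1 = 0.5, 1 and 1.5 the threshold is 0.25, 0.5 and 0.75.

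**Step 4: change against adjustment.** Variance of change minus adjusted variance = s1² + s0² − 2r·s0·s1 − s1²(1 − r²) = (s0 − r·s1)², which is never negative. So the change is never more precise than the adjusted comparison, whatever the SDs (apart from the one degree of freedom spent on the slope).

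**Step 5: the mean of four ratings.** With correlation ρ between visits, the mean has variance (1 + 3ρ)/4, which is 0.55, 0.70 and 0.85 at ρ = 0.4, 0.6 and 0.8. Unadjusted power is then about 0.97, 0.92 and 0.86, if the same average difference holds over all four weeks. Example with ρ = 0.6 and r = 0.3: mean alone 0.70; mean adjusted for day 0, 0.70 − 0.09 = 0.61; mean minus day 0, 0.70 + 1 − 0.60 = 1.10.

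**The case against.** **The two sections may not contradict each other.** Section {12} can be read as giving the instrument and schedule, and {20a} as giving the derived variable. BDI-II shows the same shift in wording. A reader might infer that {12} defines an on-treatment level which {20a} then contradicts. The document does not support that: {12} never restricts the ratings to time on the new drug, and the weekly series for arms A and B includes day 0. What stands is an ambiguity about which FIBSER variable will be compared.

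**The objective compares arms.** A reader might infer that the tolerability result itself becomes a contrast with the old drug. It does not, because day 0 cancels between the arms (step 1). The problem is limited to within-arm results.

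**A change score can be more precise.** A reader might take the loss of power at low r as established. It is an assumption: the document gives no r, and above 0.5 with equal SDs the change gains. A low r is plausible when two ratings concern different drugs, but that is a judgement. Nor can day-0 scores of zero be assumed for patients without an earlier antidepressant, since sleep medication is allowed in the run-in.

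**Early side effects are partly covered.** {20a} names no week-4 change, refers to follow-up visits in the plural and plans descriptive statistics for all variables. Treatment-related adverse events of grade 2 or above are a second tolerability endpoint, assessed weekly, with no baseline subtracted. This stands, and it lowers the weight of the point.

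None of these objections makes the within-arm change a measure of the new therapy, or gives a precision argument for subtracting day 0 rather than adjusting for it.

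**Conclusion.** The point holds in a limited form. The FIBSER endpoint is worded in two ways, and a within-arm change, which the general wording of {20a} would test, does not measure the tolerability of the newly chosen therapy. The between-arm comparison of change is unbiased. Relative to a single follow-up rating it is less precise if r is below 0.5 with equal SDs, and more precise above. Relative to the same ratings adjusted for day 0 it is never more precise.

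For scale, at 95 per arm and a difference of 0.41 SD, change has power 0.61 at r = 0.2 and 0.95 at r = 0.7, against 0.82 and 0.98 with adjustment. These figures rest on assumed values of the SDs, r and the effect. The absence of bias rests on randomisation and on the arm assignment not itself altering the day-0 rating: the footnote places that rating before the first intake, without saying whether it precedes randomisation.

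This is one of seven secondary endpoints. The primary result and the sample size are unaffected.

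**What to change.** In Outcomes {12} and Statistical methods {20a}, state one FIBSER variable: the mean of the ratings on days 7, 14, 21 and 28, compared between arms A and B with the day-0 rating as covariate. Report the weekly means by arm alongside. Bring section {20b} into line by naming this as a planned adjusted analysis. Add a sentence that a baseline-to-follow-up FIBSER test within an arm is not to be interpreted as tolerability of the new drug.

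The cost is a few sentences. All ratings are already scheduled, so no further data or patients are needed. The drawback is that an average dilutes a difference present at only one visit; the weekly means by arm would show it.

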#### Plans to promote participant retention and complete follow-up {18b}

Assessments and follow-ups are only conducted during the participants’ inpatient stay at the psychiatric clinic. Therefore, the risk of loss to follow-up and deviation to the protocol due to failure to comply with the study visits are considered negligible. However, patients who withdraw their consent (e.g., refuse further data collection) will be informed that all data collected until the time point of their withdrawal will be kept coded and used for analysis.

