#### Methods in analysis to handle protocol non-adherence and any statistical methods to handle missing data {20c}

Missing data will be retrospectively retrieved from medical records if possible. If the missing data cannot be retrieved, the last observed value will be used for analysis. Study drop-outs are replaced to achieve the final calculated study size of 95 patients per study arms A and B.

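### Time to response stops at week 4, but the only group tests named are Fisher's exact test and the t test, and neither fits that endpoint

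*Protocol article*

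**What the plan says.** In the Protocol article, Outcomes {12} defines the first secondary endpoint as "time to response—time span from the start of antidepressant pharmacotherapy until first assessed response", with observation ending at week 4. It defines another as "time till discharge—time span from admission to discharge from inpatient treatment, assessed up to 3 months".

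Statistical methods {20a} lists the outcomes to be analysed, among them "time to response, remission rate, overall change in HAM-D17 score, laytime in the clinic". It then gives one rule for group comparisons: "Fisher’s exact test or *t* test is used to compare pairwise differences between groups and between baseline and follow-up visits as per data type". The only other tools it names are descriptive statistics, the Spearman coefficient and a general remark on confounder adjustment.

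Two other sections bear on the point. Section {18b} says "Assessments and follow-ups are only conducted during the participants’ inpatient stay at the psychiatric clinic". Section {20c} says "If the missing data cannot be retrieved, the last observed value will be used for analysis". HAM-D17 is scored on days 0, 7, 14, 21 and 28 in arms A and B.

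**The concern.** A duration is not categorical, so choosing the test by data type sends time to response to the t test. Every patient then needs a number, and a patient who has not responded by week 4 does not have one. Carrying the last observed value forward can fill in a HAM-D17 score, but it does not say what time to give a patient without the event.

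Two ways remain to run the named test:

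- **Drop non-responders.** This conditions on something that happens after randomisation and that the service is meant to change. The extra responders, which are the expected benefit, enter the comparison only through how late they respond.
- **Give non-responders day 28.** Everyone stays in, but a patient who first responds at the day-28 visit gets the same value as one who never responds.

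Section {20a} also commits the investigators to justify any departure from the plan. Choosing a better method later would therefore be a declared change in an open-label trial whose HAM-D17 raters know the allocation.

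**Working it through.** **Inputs from the protocol.** Response 0.5 (standard care) and 0.7 (PGx guided), two-sided α = 0.05, power 80%, 95 per arm (Sample size {14}); weekly HAM-D17 to day 28 (Participant timeline {13}).

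**The plan's own figure.** With pooled variance and no continuity correction:

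n = [1.96·√(2·0.6·0.4) + 0.842·√(0.5·0.5 + 0.7·0.3)]² / 0.2² = (1.358 + 0.571)² / 0.04 ≈ 93 per arm.

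This is within two patients of the stated 95, so the inputs are taken as given.

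**Patients without a response time.**
- Arm B: 95 × 0.5 = 47.5.
- Arm A: 95 × 0.3 = 28.5.
- Together: 76 of 190, or 40%.

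The planning rates describe status at week 4, whereas time to response counts the first response at any weekly visit. A patient who responds in week 2 and relapses by week 4 has a response time. Under complete follow-up these shares are therefore upper bounds.

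**Assumed timing (not in the documents).** Probability of first response at days 7/14/21/28:
- Arm B: .05/.10/.15/.20 (none .50).
- Arm A, same timing: .07/.14/.21/.28 (none .30).
- Arm A, late: .05/.10/.20/.35 (none .30).
- Arm A, very late: .05/.10/.15/.40 (none .30).

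**Mean times these imply.**
- Responders in B: (0.35 + 1.40 + 3.15 + 5.60) / 0.5 = 21.0 days.
- Responders in A: same timing 14.7/0.7 = 21.0; late 15.75/0.7 = 22.5; very late 16.1/0.7 = 23.0 days.
- All patients, non-responders set to day 28: B 10.5 + 14.0 = 24.5 days. A 14.7 + 8.4 = 23.1, 15.75 + 8.4 = 24.15 and 16.1 + 8.4 = 24.5 days.

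Among responders, A looks no faster in the first scenario and slower in the other two, although 20 percentage points more patients respond. With day 28 assigned, the very late scenario shows no difference at all.

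**Simulation.** 95 per arm, 4,000 to 5,000 trials per scenario (Monte Carlo standard error at most √(0.25/4000) = 0.8 percentage points):

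| Scenario for arm A | t test, responders only | t test, non-responders at day 28 | Log-rank rejects |
|---|---|---|---|
| Same timing | rejects 5% | rejects 32%; wrong direction 0.0% | 76% |
| Late | wrong direction 21% | rejects 7%; wrong direction about 1% | 64% |
| Very late | wrong direction 33% | rejects 4–5%; wrong direction about 2% | 55% |

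**Other timing assumptions.**
- Constant hazards reaching 50% and 70% by day 28, hazard ratio ln 0.3 / ln 0.5 = 1.74: power 12% (responders only), 74% (day 28 assigned), 85% (log-rank). Schoenfeld's formula with 190 × 0.6 = 114 events gives Φ(√114/2 × ln 1.74 − 1.96) ≈ 84%, which agrees.
- Same timing in both arms, responders split .1/.3/.3/.3 over the four visits: 5%, 40% and 78%.

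The log-rank test has the highest power in every scenario. The size of its advantage depends on the timing.

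**Time till discharge.** The protocol gives no length-of-stay figure, so the share still in hospital at 3 months cannot be computed.

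**The case against.** The strongest defence is that the article does not say non-responders are dropped. If all patients were followed to day 28, a t test with non-responders set to day 28 would be a valid comparison of restricted mean times. A reader might infer that the plan is a responders-only analysis that will make a beneficial service look slower. The text does not support that. It leaves the handling open, and the 21–33% wrong-direction rate needs both a responders-only test and extra responders concentrated late. With proportional hazards from the same control rates, the responders-only test is significantly wrong in only about 0.5% of trials. This part of the defence stands. However, the day-28 version is not stated either, and it had less power than the log-rank test in every scenario tried.

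A second defence is that a journal article condenses the full plan, so a missing censoring rule is not in itself a fault. That is accepted. The point is that the article does name its between-group tests for the listed outcomes, and they do not suit this one. Fisher's exact test could compare whether patients responded, but it ignores when.

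Third, the effect on time till discharge is unquantified. Censoring there arises from stays beyond 3 months or withdrawal and may be small. That also stands, so discharge is secondary to this point.

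**Conclusion.** The concern holds for time to response. The stated rule leads to a t test on an endpoint for which up to about 40% of randomised patients (50% of arm B, 30% of arm A) may have no value. Across the assumed timings that favour a real difference in restricted means or in hazards, the cost is a large loss of power: for example about 5% or 32% against 76% when responders in both arms share the same timing. A significant result in the wrong direction is possible, but only under a responders-only reading with late extra responders.

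It would be wrong to infer that the trial's main conclusion is at risk. The primary endpoint is binary response at day 28, Fisher's exact test suits it, and the sample size rests on it alone. Nor do the documents show that the comparison of hospital stay is materially distorted. The point therefore should be fixed, but it is not critical. The power figures rest on assumed weekly timings, the protocol's 0.5 and 0.7, and complete follow-up to day 28.

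**What to change.** In {20a}, state that time to response is analysed in all patients randomised to arms A and B with Kaplan-Meier curves and a log-rank test, or with a discrete-time model suited to the weekly visits. Report an effect estimate such as a hazard ratio or a difference in restricted mean time. Censor patients without a response at day 28, or at their last HAM-D17 if earlier.

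Because assessments end at discharge, leaving before day 28 may be related to how well the patient is doing, and that censoring may be informative. Add a sensitivity analysis for these patients.

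Use the same approach for time till discharge, censored at 3 months. The gain there cannot be stated without a length-of-stay figure.

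The cost is a few sentences and a little more analysis work. No new data are needed, and the sample size and primary analysis do not change.

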### Trial design {8}

This is an open-label, randomized controlled trial, investigating the effectiveness and tolerability of registered antidepressants in adult inpatients with diagnosed major depressive episode.

To prevent selection bias, eligible patients in need of a new antidepressant pharmacotherapy are randomized at the same ratio into either the control or the intervention arm (parallel study arms).

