#### Sample size {14}

The sample size was calculated to be 95 patients per study arms A and B. This was done taking into account the following criteria: power = 80%, *α* = 5%, response rate standard care = 0.5 [1, 2] and response rate PGx guided = 0.7 [16]. For the observational study arm, there is no sample size calculation needed, since this arm does not contribute to the primary endpoint.

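### Fisher's exact test is named for baseline-versus-follow-up comparisons, where it is invalid; the t test is not specified as paired; and within-arm tests do not answer the between-arm question

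*Protocol article*

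**What the plan says.** All test assignments stand in one sentence of the protocol article, under Statistical methods for primary and secondary outcomes {20a}. It offers Fisher's exact test or the t test and says that the test "is used to compare pairwise differences between groups and between baseline and follow-up visits as per data type". No other test for a difference is named. The same section adds "Significance level is two-sided", with alpha 0.05, and lists changes in HAM-D17, BDI-II and FIBSER among the secondary outcomes.

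The hypothesis concerns the arms. Under Objectives {7} the null is that "Therapy response rates after antidepressant treatment for 4 weeks do not differ" according to whether the pharmacist-guided PGx service was applied, and the secondary objectives also compare the arms.

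The Participant timeline {13} has HAM-D17 and FIBSER scored on days 0, 7, 14, 21 and 28, and BDI-II on days 0, 14 and 28, in the same patients. Section {20b} says that no adjusted analyses are currently planned, while {20a} mentions adjustment for confounders only for unspecified further analyses.

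**The concern.** One pair of tests is given two jobs. Between arms the observations come from different patients, and both tests fit. Between baseline and follow-up each patient supplies both values. Fisher's exact test ignores that link and is not valid for it; a binary comparison across visits needs a paired test such as McNemar's. The t test has a paired form, but the sentence does not say which form is meant.

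The second issue is the target. Patients in both arms start a new antidepressant at day 0, so improvement is expected in both. A p-value for change within an arm mixes that improvement with any effect of PGx. Such p-values also invite the argument that one arm improved significantly and the other did not, which is not evidence of a difference between them. What is at stake is the reporting of the secondary scores, not the primary endpoint.

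**Working it through.** **The plan's own figure.** Sample size {14}: "The sample size was calculated to be 95 patients per study arms A and B", from rates 0.5 and 0.7, 80% power and alpha 5%. With the pooled-variance formula for two proportions, two-sided and 1:1:

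n = [1.96·√(2·0.6·0.4) + 0.842·√(0.5·0.5 + 0.7·0.3)]² / 0.2² = (1.358 + 0.571)² / 0.04 ≈ 93 per arm.

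This is close to 95; power at 95 by the same approximation is 0.808. The figure concerns the between-arm primary comparison and does not depend on the point made here. It only supplies n = 95 below.

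**Where Fisher's exact test could meet paired binary data.**
- Response is a HAM-D17 reduction of at least 50% from day 0, so it has no day-0 value.
- Remission is HAM-D17 of 8 or less ({12}); entry requires 17 or more ({10}). Entry is scored before day 0, so a day-0 remitter is possible but should be rare.
- Adverse events have no day-0 assessment in Table 1.

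No binary outcome therefore has a usable baseline state.

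**The t test, if it were run unpaired.** The protocol gives no within-patient correlation ρ, so these values are assumptions, with equal variances at both visits and n = 95 in one arm. The standard error is too large by the factor 1/√(1−ρ). The true two-sided size is about 2·[1 − Φ(1.973/√(1−ρ))], where 1.973 is the t critical value on 188 degrees of freedom. Power is for an assumed change of 0.3 SD.

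| ρ | SE factor | True size | Power unpaired | Power paired |
|---|---|---|---|---|
| 0.3 | 1.20 | 0.018 | 0.55 | 0.69 |
| 0.5 | 1.41 | 0.005 | 0.55 | 0.83 |
| 0.7 | 1.83 | 0.0003 | 0.57 | 0.96 |

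The error is conservative throughout. For a large change it alters no conclusion: an assumed fall of 8 points with SD of change 7 gives a paired t of 8/(7/√95) = 11.1, and dividing by the SE factors leaves about 9.3, 7.9 and 6.1.

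**Within-arm significance as evidence on PGx.** Suppose that the arms are equally effective and that each has probability w of a significant change of its own. Exactly one arm is then significant in 2w(1−w) of trials: 50% at w = 0.5, 32% at w = 0.8, 18% at w = 0.9. The risk is greatest for modest changes; with a t near 11 both arms are significant whatever PGx does.

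**Gain from adjusting for day 0.** With common variance σ² and correlation ρ, the per-patient variance is 2σ²(1−ρ) for a change score and σ²(1−ρ²) after adjustment for day 0. The ratio is (1+ρ)/2:
- ρ = 0.3: 0.65, a reduction of 35%
- ρ = 0.5: 0.75, a reduction of 25%
- ρ = 0.7: 0.85, a reduction of 15%

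If the day-0 SD is k times the day-28 SD, the saving is (k−ρ)² in units of the day-28 variance. It can shrink to zero, but in large samples it is never negative.

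**The case against.** The strongest reply is that the sentence can be read sensibly. A paired t test is a t test, the sentence speaks of pairwise differences, and the choice follows data type. On that reading scores get a paired t test across visits, and Fisher's exact test serves binary outcomes between arms. A condensed article may leave the form of the t test to a fuller plan. This stands: a reader might infer that every within-arm p-value will be wrong, and the text does not support that, because no independent-samples version is named.

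A reader might also infer that within-arm tests replace the randomised comparison or will be used to claim a PGx effect. The documents do not say so. The between-arm comparison is in the same sentence, the objectives are between arms, and comparing the listed changes between groups is a valid randomised contrast without adjustment. Within-arm description also has a use in the observational arm, which has no randomised comparator.

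What the reply does not remove is that, as worded, Fisher's exact test covers a paired comparison with no paired binary alternative named, and that significance tests of change within an arm are planned although they do not bear on the hypothesis.

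**Conclusion.** The point holds in limited form. Naming Fisher's exact test for baseline versus follow-up is an error, with little practical reach because no binary outcome has a usable day-0 state. For the t test the fault is an unspecified form; the size and power figures apply only if the unpaired form is used, rest on assumed correlations of 0.3 to 0.7, and err on the conservative side. Within-arm tests are off target, and the 32% figure (at 80% power per arm) shows why contrasting their significance would mislead; that is a risk of misuse, not a stated intention. The primary between-arm test and the sample size are untouched.

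The practical gain lies in the secondary scores: a variance reduction of about 35% to 15% relative to change scores over the same assumed correlations, with equal variances at day 0 and day 28. That is an improvement in precision, not the repair of an invalid between-arm analysis.

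**What to change.** Amend the test sentence in {20a} before analysis:

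1. Limit Fisher's exact test to binary comparisons between arms A and B.
2. Report within-arm change descriptively, as mean change with 95% CI. If a within-arm test is kept, name the paired t test or the Wilcoxon signed-rank test for scores and McNemar's test for binary data.
3. Draw conclusions on HAM-D17, BDI-II and FIBSER from the between-arm difference adjusted for the day-0 score (ANCOVA) instead of an unadjusted t test, and align {20b}, which now says that no adjusted analyses are planned.

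The cost is one rewritten sentence and a matching line in {20b}. The day-0 scores are already in the schedule, so no new data, visits or patients are needed. Making the change before analysis also avoids having to justify it as a deviation in the final report.
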